# Supine vs upright exercise in patients with hepatopulmonary syndrome and orthodeoxia: study protocol for a randomized controlled crossover trial

**DOI:** 10.1186/s13063-021-05633-7

**Published:** 2021-10-09

**Keywords:** Hepatopulmonary syndrome, Orthodeoxia, Exercise tolerance, Randomized controlled trials, Liver transplantation

## Abstract

**Background:**

The hepatopulmonary syndrome (HPS) is a pulmonary complication of liver disease found in 10 to 32% of patients with cirrhosis and is characterized by intrapulmonary vascular dilatations and abnormal oxygenation. Liver transplantation is the only effective therapy for this disease. Patients with HPS have significant exercise limitations, impacting their quality of life and associated with poor liver transplant outcomes. Many patients with HPS exhibit orthodeoxia—an improvement in oxygenation in the supine compared to the upright position. We hypothesize that exercise capacity will be superior in the supine compared to the upright position in such patients.

**Methods:**

We propose a randomized controlled crossover trial in patients with moderate HPS (PaO_2_ < 80 mmHg) and orthodeoxia (supine to upright PaO_2_ decrease > 4 mmHg) comparing the effect of supine vs upright position on exercise. Patients with pulmonary hypertension, FEV1/FVC ratio < 0.65, significant coronary artery disease, disorders preventing or contraindicating use of a cycle ergometer, and/or moderate or severe ascites will be excluded. Participants will be randomized to cycle ergometry in either the supine or upright position. After a short washout period (a minimum of 1 day to a maximum of 4 weeks), participants will crossover and perform an exercise in the alternate position. Exercise will be performed at a constant work rate of 70–85% of the predicted peak work rate until the “stopping time” is reached, defined by exhaustion, profound desaturation, or safety concerns (drop in systolic blood pressure or life-threatening arrhythmia). The primary outcome will be the difference in the stopping time between exercise positions, compared with a repeated measures analysis of variance method with a mixed effects model approach. The model will be adjusted for period effects. *P* < 0.05 will be considered statistically significant.

**Discussion:**

HPS patients have hypoxemia leading to significant exercise limitations. If our study is positive, a supine exercise regimen could become a routine prescription for patients with HPS and orthodeoxia, enabling them to exercise more effectively. Future studies could explore the corresponding effects of a supine exercise training regimen on physiologic variables such as long-term exercise capacity, quality of life, dyspnea, and liver transplantation outcomes.

**Trial registration:**

ClinicalTrials.gov Protocol Registration and Results System (PRS) NCT04004104. Registered on 1 July 2019

**Supplementary Information:**

The online version contains supplementary material available at 10.1186/s13063-021-05633-7.

## Background

The hepatopulmonary syndrome (HPS) is a pulmonary complication of liver disease found in 10 to 32% of patients with cirrhosis [1]. It is defined by the combination of [1] liver dysfunction or portal hypertension, [2] intrapulmonary vascular dilatations, and [3] abnormal oxygenation [2]. Liver transplantation is the only known effective therapy for this disease [3].

### Exercise in the hepatopulmonary syndrome

Participants with liver disease have reduced exercise capacity compared to normal controls [measured by peak oxygen consumption (VO_2peak_)] [4, 5] due to a combination of deconditioning, malnutrition-associated muscle weakness, and anemia [6]. Exercise tolerance is further impaired in patients with HPS [7–9], who have more dyspnea and a reduced New York Heart Association functional class, compared to patients with cirrhosis who do not have HPS [10]. Formal exercise testing data are available in four small reports and one large cross-sectional study and demonstrate reduced exercise capacity and profound exercise desaturation in HPS (Table 1). The authors have hypothesized that this exercise desaturation is the result of increased shunt physiology, worsening diffusion due to increased pulmonary blood flow with reduced capillary transit time (a physiologic phenomenon called the “diffusion-perfusion defect”), and a reduced mixed venous oxygen content, the impact of which on arterial oxygen saturation is magnified by the former two effects [9]. These studies support the concept that an abnormal pulmonary circulation contributes to exercise limitation in HPS and that patients with HPS experience severely reduced aerobic capacity, beyond that found in those with cirrhosis without HPS [7–9, 11, 12].

**Table 1 Tab1:** Previous literature reporting exercise testing in patients with HPS

Study		Exercise findings
Thorens et al., 1992 [11]	HPS case report (*n* = 1); constant work rate test*	• Worsening physiologic shunt (from 12% at rest to 26% with exercise)
Epstein et al., 1998 [7]	HPS (*n* = 5) vs cirrhosis^†^ (*n* = 19); incremental cycle ergometry	• Reduced VO_2peak_ (55% predicted in HPS vs 72% predicted in cirrhosis) • Progressive exercise hypoxemia • Earlier onset of the anaerobic threshold • Elevated dead space ventilation
Whyte et al., 1998 [9]	HPS (*n* = 8); incremental cycle ergometry	• Progressive exercise desaturation • Diminished achieved workload (mean 48% predicted) • Reduced mixed venous oxygen content
Nusair et al., 2005 [8]	HPS case report (*n* = 1); incremental cycle ergometry	• Reduced VO_2peak_ (41% predicted) • Progressive exercise hypoxemia • Marked dyspnea • Worsening physiologic shunt
Faustini-Pereira et al., 2015 [12]	HPS (*n* = 92) vs cirrhosis^‡^ (*n* = 86); modified Bruce protocol*	• Reduced VO_2peak_ (80.2% predicted in HPS vs 86.7% predicted in cirrhosis) • Reduced 6-min walk distance (341 m in HPS vs 416 m in cirrhosis)

*HPS* hepatopulmonary syndrome, *VO*_*2peak*_ maximum rate of oxygen consumption measured during incremental exercise, *m* meters

*Exercise modality not specified

^†^“Cirrhosis” defined as PaO_2_ ≥ 90 mmHg and alveolar-arterial oxygen gradient < 20 mmHg (negative contrast echo not required)

^‡^“Cirrhosis” defined as alveolar-arterial oxygen gradient < 20 mmHg (negative contrast echo not required)

### Orthodeoxia in the hepatopulmonary syndrome

Intrapulmonary vascular dilatations (IPVDs) are believed to cause the hypoxemia of HPS through a “diffusion-perfusion defect” [11]. This is a combination of an increased distance between the alveolar membrane and the red blood cells in the center of dilated capillaries, causing an effective diffusion abnormality, along with a reduced resistance to flow causing increased perfusion through the dilated capillaries—which reduces available time for equilibration between the alveolar gas and the blood [13]. These IPVDs are often most prominent at lung bases [14]. Accordingly, due to the gravitational redistribution of blood flow to the lung bases in the upright position, there is an increase in blood volume passing through IPVDs, resulting in a worsening diffusion-perfusion defect when moving from the supine to the upright position [15]. A corresponding drop in partial pressure of arterial oxygen (PaO_2_) of greater than 5% or 4 mmHg in the upright compared to the supine position is called orthodeoxia [1]. This is often associated with a perception of increased dyspnea when upright called platypnea [14].

### Study rationale and purpose

Limited current physiologic data suggest an important role for hypoxemia in the exercise limitation caused by HPS, suggesting that HPS patients with orthodeoxia may have a greater exercise capacity when exercising in the supine position compared to the conventional upright position. Previous studies have compared upright to supine exercise in various populations. In healthy individuals, although cardiac output increases in the supine exercise due to an increased preload and stroke volume [16–18], there is also reduced blood flow to the leg muscles [19], resulting in reduced muscle oxygen uptake, more profound muscle deoxygenation [20], and a lower anaerobic threshold [19] compared to the upright exercise. In patients with comorbidities, supine exercise has generally been found to worsen physiologic parameters compared to upright exercise, including a drop in alveolar ventilation (with an increase in partial pressure of end tidal CO_2_) [21] in patients with chronic obstructive pulmonary disease (COPD), a failure to increase left ventricular ejection fraction in patients with hypertension [22], and ST segment depression possibly indicating a lower ischemic threshold in patients with coronary artery disease [23]. However, positional effects on exercise in patients with HPS, and the unique impact of orthodeoxia have not been reported.

The primary aim of our study is to evaluate the effect of the supine position on exercise in HPS participants with orthodeoxia, compared to exercise in the upright position.

## Methods and design

### Objective and hypothesis

Our primary objective is to study the effect of supine position, compared to the upright position, on exercise parameters in participants with HPS and orthodeoxia. We hypothesize that these participants will have improved exercise time when supine, compared to upright.

### Trial design

This will be a randomized controlled crossover trial, conducted in the Canadian HPS Program [an HPS clinical and research program founded in 2005 (www.hpscare.com), consisting of sites in Toronto, Ontario (Unity Health Toronto and University Health Network), and Montreal, Quebec (Centre hospitalier de l’Université de Montréal)]. Eligible participants will be identified by clinicians in the Canadian HPS Program through the existing Canadian HPS Program Database (a database of all HPS patients seen in the Canadian HPS Program who have consented for data collection and to be approached for future research). Once patients have provided assent to the clinician, they will be contacted by independent research personnel, either by phone or in-person during clinic visits, to seek informed consent (see Additional file 1 for the consent form). Consenting patients will be randomized to start with either a supine or upright exercise test on a bicycle ergometer. Subsequently, participants will complete the alternate test on a separate day, within 4 weeks of the first test (Fig. 1). The allocation sequence will be generated by a research coordinator in advance, through a computerized random number generator. This research coordinator will assign the testing order for each newly recruited participant, and only this person will have access to the allocation sequence, which will remain concealed from study investigators at all times.

**Fig. 1 Fig1:**
[figure not shown]
Study design

### Participants

Participants will be sequentially recruited from the Canadian HPS Program Database between late 2019 and approximately mid-2023 (including a pause due to SARS-COV-2 for much of 2020). The eligibility criteria are outlined in Table 2. The drop-out criteria are provided under the “Exercise protocol” section.

**Table 2 Tab2:** Eligibility criteria

**Inclusion criteria** 1. Moderate HPS: (a) Liver disease (evidence of synthetic liver dysfunction and/or portal hypertension on biochemistry and/or imaging) (b) Moderate hypoxemia ▪ PaO_2_ < 80 mmHg ▪ AaDO_2_ ≥ 15 mmHg or ≥ 20 mmHg if age > 64 [1] (c) Intrapulmonary vascular dilatations (microbubbles seen in the left heart ≥ 3 cycles after the right heart on saline contrast echocardiography) 2. Presence of orthodeoxia (PaO_2_ decrease by > 4 mmHg when the patient moves from supine to upright position) **Exclusion criteria** 1. Pulmonary hypertension (a) Echocardiographic estimated right ventricular systolic pressure ≥ 50 mmHg (b) Right heart catheterization mean pulmonary artery pressure > 25 mmHg with pulmonary capillary wedge pressure ≤ 15 mmHg 2. Significant obstructive ventilatory impairment (FEV1/FVC ratio < 0.65) [14] 3. Known significant coronary artery disease 4. Significant neurologic, orthopedic, or rheumatological disorders preventing the use of a cycle ergometer 5. Other absolute contraindications to submaximal exercise testing [24] (a) Uncontrolled cardiac arrhythmia with hemodynamic compromise (b) Symptomatic severe aortic stenosis (c) Decompensated heart failure (d) Acute cardiopulmonary illness (e.g., venous thromboembolism, myocarditis, pericarditis, endocarditis, acute aortic dissection) 6. Moderate or severe ascites	

*PaO*_*2*_ partial pressure of arterial oxygen, *FEV1/FVC* forced expiratory volume in 1 s over forced vital capacity, *AaDO*_*2*_ alveolar-arterial oxygen gradient [PAO_2_ − PaO_2_, where PAO_2_ = [FiO_2_ (*P*_atm_ − *P*_H2O_) − PaCO_2_/0.8]], *AO*_*2*_ partial pressure of alveolar oxygen, *FIO*_*2*_ inspiratory oxygen fraction, *P*_*atm*_ atmosphere pressure, *P*_*H2O*_ water vapor partial pressure, *PaCO*_*2*_ arterial carbon dioxide pressure

### Exercise protocol

Each participant will perform a constant work rate exercise test (CWRET). The constant work rate will be individualized for each participant and set at 70–85% of their estimated peak work rate [25], targeting an estimated test duration of 180–480 s (to increase the chances that exercise limitation is due to the physiologic effects of exercise rather than physical discomfort or boredom [26]). Peak work rate will be estimated from a previous room air 6-min walk test (6MWT) performed within the last 6 months (peak work rate = 0.168 × 6MWD (m) − 4.085) [27].

The CWRET will include a warmup period consisting of 1 min of rest during which participants will be in set position with their feet planted on the pedals, without pedaling. This will be followed by an immediate ramp-up to the predetermined target constant work rate [25, 26]. Patients will be instructed to pedal at a rate between 50 and 60 revolutions per minute (rpm) and will be provided with constant feedback on pedaling frequency through a biofeedback display. We will also provide standardized verbal encouragement throughout [28], relating when they are above or below the target pedaling frequency, congratulating them when they are within the target frequency, and encouraging them to continue pedaling for as long as they feel able to. For each participant, exercise in each position will be standardized with respect to the proper seat adjustment relative to leg length and pedaling cadence. Upright cycle ergometry will be performed on the Corival Ergometer Bicycle (LODE B.V. Medical Technology Groningen, the Netherlands) at an angle of 90°. The supine cycle will be performed on the Stress EchoBed® (Medical Positioning Inc., USA) at an angle of 0°. For both tests, all measurements will take place through a pitot tube spirometer. Volume and flow calibrations (pitot tube spirometer) and gas calibration (Ergo Card Analyzer, Medisoft, USA) will be performed within 1 h of the exercise test, and Bio calibration will be performed on the pitot tube spirometer every 3 months.

Inspiratory capacity will be measured before and after exercise. Before, after, and throughout exercise, we will measure the following: oxygen uptake (VO_2_) and carbon dioxide production (VCO_2_) (measured breath-by-breath, averaged over 30-s epochs), oxygen saturation and heart rate (continuously, by pulse oximetry and 12-lead electrocardiography, respectively), blood pressure (every 2 min, by manual sphygmomanometry), and subjective dyspnea and leg fatigue (every 1 min, by modified Borg scale) [29]. Participants will continue exercising until they reach one of the following stopping criteria: 1) the point at which, after standardized encouragement, the participant is unable to continue because of symptoms (i.e., participant does not wish to continue or is unable to maintain a minimum peddling frequency of 40 rpm for ≥ 10 s) [defined as the “tolerable limit” (tLIM)]; 2) desaturation below a set point for ≥ 30 s; 3) a drop in systolic blood pressure by ≥ 10 mmHg from baseline; or 4) the appearance of life-threatening arrhythmias (such as significant ventricular arrhythmias or high-grade heart block). The low saturation set point will be chosen individually for each participant, as the lower of 80% [26], or the nadir desaturation seen on baseline room air 6MWT. Stopping time will be defined as the duration of pedaling during the constant workload exercise test before a stopping criterion was met. During the test, the stopping time and criterion will be determined by agreement between the PI and the experienced technician conducting the test. Upon agreement, the time and criterion will be designated within the CPET software and independently recorded on a data collection sheet by a research assistant (the assistant will also use a stopwatch during the test to independently record timing, ensuring that stopping time is measured in duplicate to account for any system failures or errors). The dropout criteria for this study include unwillingness/inability to return for the second test or presence of one of the arrhythmic or hemodynamic-related stopping criteria on the first of the protocolized exercise tests (a safety-related dropout).

Participants will be reminded to bring running shoes and comfortable exercise clothes, to ensure that they have eaten before the test, to take all usual medications, and to avoid major exercise for 24 h before the test. A physician with expertise in cardiopulmonary exercise testing will be in attendance for monitoring throughout test procedures. Given the small sample size and the high relative safety of the exercise intervention, we will not be performing official interim analyses or creating a data and safety monitoring board. However, if any safety event occurs during study conduct, the investigators will immediately re-evaluate the safety of the protocol and overall study. Upon completion, patients will not only be notified of the overall study results and publication, but also of their individual performance and whether supine exercise was found to be beneficial in their case.

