### Outcome measures

Exercise tests will be analyzed by a pulmonologist with experience in cardiopulmonary exercise test interpretation. This assessor will be masked to exercise position.

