### Primary outcome measure

The primary outcome will be the difference in stopping time between the upright and supine exercise positions. We will exclude participants who stopped the exercise test due to either life-threatening arrhythmia or a drop in systolic blood pressure from the primary outcome analysis.

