### Auditing and data management

Each step of the study process, including test conduct, data recording, and data analysis, will be conducted through the guidance of standard operating procedures (SOPs). A research coordinator and the PI will be present at each exercise study to audit and ensure compliance of the test conduct and data recording with SOPs. A linking log will be used to track the recruitment of participants into the study. Participant personal health information (PHI) such as full name, date of birth, MRN, email, and phone number will be collected and stored within the master linking log. All participants will be assigned a study ID (matching their Canadian HPS Program Database ID), which will be used alongside the rest of the results. The linking log will be separately and securely stored on an institutional drive for 5 years post-study closure, after which it will be destroyed. Only designated research personnel will have access to the data. The de-identified dataset will be stored for a period of 7 years after study completion.

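### Stopping time and criterion are called during the test by staff who can see the position, and the article describes no masked confirmation of this primary outcome

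*Protocol article*

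**What the plan says.** Primary outcome measure: "The primary outcome will be the difference in stopping time between the upright and supine exercise positions".

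The Exercise protocol section says who fixes that time and when. During the test, "the stopping time and criterion will be determined by agreement between the PI and the experienced technician conducting the test". It continues: "Upon agreement, the time and criterion will be designated within the CPET software". A research assistant also records the result on a data sheet and runs a stopwatch. The stated reason for the duplicate timing is protection against equipment faults or mistakes.

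The same section gives numeric rules for two of the stopping criteria: cadence under 40 rpm for at least 10 s, and saturation under an individual set point for at least 30 s. The participant may also simply choose to stop. Encouragement is standardized.

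On masking, Outcome measures has two sentences: "Exercise tests will be analyzed by a pulmonologist with experience in cardiopulmonary exercise test interpretation", and "This assessor will be masked to exercise position".

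The criterion matters as well as the time. Under Primary outcome measure, participants who stopped for arrhythmia or a fall in systolic pressure are left out of the primary analysis. Under Exercise protocol, such a stop on the first test is a safety dropout.

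**The concern.** Participants cannot be masked to whether they are lying or sitting, so the observers' call is the one part of the outcome measurement that masking could protect. The article names a masked assessor, and does so directly above the primary outcome. Yet it assigns the primary outcome to two people in the room, and the trial's hypothesis is that supine time will be longer.

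If those people allow slightly more time in one position before calling the stop, the within-person difference moves by that amount. Randomizing the order does not remove such an error, because it follows position and not period. The same call fixes the criterion, and so who stays in the primary analysis. With a target of 10 participants, one reclassification affects 1/10 = 10% of the sample.

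**Working it through.** The article states no figure for this point, so the check is mainly a comparison of its sections.

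**1. Are the bedside staff unmasked?** The article does not say so in words, but the inference is secure.
- The technician conducts the test.
- On the PI, Auditing and data management says: "A research coordinator and the PI will be present at each exercise study to audit and ensure compliance of the test conduct and data recording".
- The two set-ups cannot be confused. The upright test uses an ergometer at 90°. For the other, "The supine cycle will be performed on the Stress EchoBed® (Medical Positioning Inc., USA) at an angle of 0" degrees.

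**2. Does the masked role reach stopping time?** Outcome measures gives the pulmonologist the analysis of the tests. No section has this person set, check or revise the stopping time or criterion. The one explicit assignment of that task is to the PI and technician.

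**3. Do the other safeguards mask the call?**

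| Safeguard | What it limits | Masks the call? |
|---|---|---|
| Agreement of two people | Individual error | No, both see the position |
| Numeric rules (10 s, 30 s) | Room for judgement | No |
| Standardized encouragement | Variation in effort | No |
| Duplicate stopwatch and data sheet | Equipment or recording error | No |

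**4. Is there latitude within the rules?** Stopping time is the pedaling time before a criterion was met. With a 10 s or 30 s window, that can mean the start or the end of the window, so up to 10 s or 30 s depends on the reading. This need not cancel within a participant. The Safety section expects many patients to reach 80% saturation at rest or with minimal effort when upright, so desaturation stops may be commoner in that position.

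**5. Scale, under an assumption.** Planned test duration is 180–480 s (Exercise protocol). The target difference is 2.85 min = 2.85 × 60 = 171 s (Recruitment and power). No document supports a particular observer shift; 15–30 s is assumed for illustration.
- Share of a test: 15/480 = 3%; 30/180 = 17%.
- Share of the target difference: 15/171 = 9%; 30/171 = 18%.

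The 171 s is used here only as a yardstick. Whether it follows from the stated standard deviation is a separate question and has no bearing on masking.

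**6. Can masked reading be done?** Saturation is recorded continuously, so the 30 s rule can be re-applied afterwards. Cadence is shown on a biofeedback display, but the article does not say that it is stored. The two positions use different devices, so export from each must be confirmed. There would be 10 × 2 = 20 tests.

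**The case against.** Staff must be able to end a test at once for safety, so a bedside call is unavoidable. The rules are largely numeric, two people must agree, and records are duplicated, so the room for judgement is narrow. The article is a condensed text, and the standard operating procedures it mentions for test conduct, recording and analysis are not shown. They may give the masked reader a part in this.

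Much of that stands. It limits the point to the absence of a described masked confirmation. It does not remove it, because the article does more than stay silent: it assigns the determination to the bedside pair. Stopping a test for safety and deriving the analysed time can also be done by different people.

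A reader might infer more than the documents support:
- **That the bedside time is final, or that the masking statement is a false assurance.** The article says only that the time is designated in the software and recorded. It neither describes nor rules out later review.
- **That the result will be biased towards supine.** The observers know the position and the hypothesis. That creates an opportunity and is not evidence of a shift.
- **That 15–30 s is an estimate of bias.** It is an assumption.
- **That masked reading would protect the whole outcome.** It can correct a late call on a numeric rule. It cannot recover time lost when a test was ended early, alter a participant's own choice to stop, or undo uneven encouragement. Blood pressure is taken manually every 2 min, so there is no continuous trace from which to re-read that criterion.

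**Conclusion.** The point holds in a limited form. Stopping time and criterion, which are the primary outcome and a basis for exclusion from its analysis, are determined by people who see the position. The masking under Outcome measures is not shown to reach them. The existing safeguards reduce error without masking the call.

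The size and direction of any bias are unknown. The 3–17% of a test and 9–18% of the 171 s target rest wholly on the assumed 15–30 s shift. The conclusion rests on one inference, that staff in the room know the position, and on the article as it stands. The benefit of masked reading is confined to stops under the numeric rules, whose share of the 20 tests is unknown. This is an inexpensive improvement to the primary endpoint, not a demonstrated flaw in the results.

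**What to change.** 1. Keep the bedside call for safety, unchanged, and record its time and criterion.
2. Have the masked pulmonologist already in the plan confirm or derive the analysed stopping time and criterion from recordings with position removed, applying the written rules. Use the continuous saturation trace for the 30 s rule. Use the cadence trace for the 10 s rule if the sponsor confirms that it is stored and can be exported from both devices. Otherwise use the time pedaling ceased.
3. State whether the time is taken at the start or the end of the 10 s or 30 s window.
4. Report agreement between the masked and bedside times, and use the bedside time in a sensitivity analysis.
5. If this is not feasible, state under Outcome measures that masking does not cover stopping time.

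The cost is export and reading of about 20 recordings by an assessor already named, plus a check of what each device stores and whether its output can be made position-free. No visit, procedure or safety rule changes.
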